#### Biobanking procedures

2.4.5

The primary mechanistic hypothesis is that gut dysbiosis and/or breast milk composition modulate neuroinflammatory pathways and long-term neurodevelopmental outcomes. Planned analyses include 16S rRNA microbiome profiling and targeted cytokine/chemokine assays (e.g., IL-6, IL-1β, TNF-α).

Biological samples will be collected three times: within 48 h of diagnosis, at 7 days post-diagnosis, and prior to discharge.
Samples: 5–8 grams of stool and 3–5 mL of breast milk.Procedure: Samples will be stored initially at −20 °C at the collection site and transferred to a centralized −80 °C freezer at Shenzhen Children's Hospital for long-term storage.Long-term storage governance: samples will be stored for up to 10 years. Access requires approval by a Biobank Access Committee. Separate informed consent will be obtained for any future genetic or exploratory analyses beyond the primary aims. As a constructive addition, residual serum from routine clinical blood draws will be collected for exploratory analysis of neuronal injury biomarkers (e.g., S100B).

#### Long-term follow-up assessment schedule

2.4.6

Follow-up assessments will occur at corrected ages of 6 months, 18 months, 3 years, and 5 years. A schedule detailing the assessments and measures taken at each time point is summarized in Table 1.

**Table 1 T1:** Schedule of long-term follow-up assessments.

Assessment	6 Months	18 Months	3 Years	5 Years
Bayley Scales of Infant and Toddler Development, Fourth Edition, Chinese Version (Bayley-4C)	✓	✓	✓	✓
Growth metrics (weight, length/height, head circumference)	✓	✓	✓	✓
Neurological examination	✓	✓	✓	✓
Seizure/epilepsy assessment	✓	✓	✓	✓
Epilepsy medication review			✓	✓
Video-EEG			✓	✓
Cranial MRI (3T)			As needed	As needed
Cognitive, language, and behavioral assessment			✓	✓
Learning disability assessment				✓
Attention problems assessment				✓
Social adaptation assessment				✓
Final outcome confirmation (cerebral palsy, cognitive impairment, epilepsy)				✓

✓, assessment performed; MRI performed only when clinically indicated. All ages are corrected ages. Bayley-4C, Bayley Scales of Infant and Toddler Development, Fourth Edition, Chinese Version; EEG, electroencephalography; MRI, magnetic resonance imaging.

### Outcome measures

2.5

#### Primary outcomes

2.5.1

Registry-based incidence of neonatal strokes in Shenzhen.

#### Secondary outcomes

2.5.2

Survival status at hospital discharge and throughout the 5-year follow-up period.Neurodevelopmental outcomes at 5 years were defined as a composite based on Bayley-4C scores and clinical diagnoses of impairments (e.g., cerebral palsy, epilepsy).Risk factor characterization (prenatal, perinatal, and postnatal).Performance of the developed prognostic prediction model for adverse neurodevelopmental outcomes.

### Sample size calculation

2.6

Assuming a 30% neurodevelopmental outcome rate at 5 years (based on published literature), a final sample of approximately 210 evaluable participants would yield 60–80 outcome events. With a maximum of 6–8 candidate predictors, this yields an events-per-variable ratio of approximately 10, exceeding the recommended minimum for logistic regression to avoid overfitting. Internal validation will be performed using bootstrap resampling (1,000 repetitions) to estimate optimism-corrected performance. Total enrollment of 300 accounts, with 10% mortality and 20% loss to follow-up, and the understanding that the final evaluable sample will be approximately 210 participants.

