#### Secondary objectives

2.1.2

To characterize the clinical presentation, short-term treatment efficacy, and safety of the three subtypes of neonatal stroke: arterial ischemic stroke, cerebral sinovenous thrombosis, and hemorrhagic stroke.To identify significant prenatal, perinatal, and postnatal risk factors for neonatal stroke, and to develop and validate predictive models for risk stratification using a panel of early biochemical and imaging biomarkers.To analyze regional and institutional variations in the diagnostic, therapeutic, and rehabilitative management of neonatal stroke, and to propose evidence-based strategies for optimizing care and standardizing treatment protocols.

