### Statistical analysis plan

2.7

All analyses will be performed using SPSS (Version 27.0) and R (Version 4.4.1).
Descriptive Statistics: Continuous data will be presented as means ± SD (for normally distributed data) or as medians [IQR] (for non-normally distributed data). Categorical data will be analyzed using Chi-square or Fisher's exact tests.Incidence and Survival Analysis: Registry-based incidence and survival rates will be stratified by gestational age, sex, birth weight, and hospital level.Predictive Model Development:
Predictor Selection: LASSO regression will be used to identify potential predictors.Model Building: Multivariable logistic regression will identify independent factors associated with poor neurodevelopmental outcomes.Model Validation: Internal validation using bootstrap resampling (1,000 repetitions) will assess model performance (discrimination, calibration, and clinical utility).A two-sided *p*-value < 0.05 will be considered statistically significant.

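### The stated 30% outcome rate gives 63 events, so the events-per-variable ratio is 10.5 to 7.9 for 6 to 8 candidate predictors, and no shrinkage of the final model is described

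*Protocol article*

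**What the plan says.** Section 2.6 of the protocol article derives the evaluable sample from enrolment: "Total enrollment of 300 accounts, with 10% mortality and 20% loss to follow-up", so that "the final evaluable sample will be approximately 210 participants". It assumes that 30% of these children have the neurodevelopmental outcome at 5 years and states that "a final sample of approximately 210 evaluable participants would yield 60–80 outcome events". From this it draws the adequacy claim: "With a maximum of 6–8 candidate predictors, this yields an events-per-variable ratio of approximately 10, exceeding the recommended minimum". The minimum is not given as a number.

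Section 2.7 sets out the modelling in two steps. First, "LASSO regression will be used to identify potential predictors". Then, "Multivariable logistic regression will identify independent factors associated with poor neurodevelopmental outcomes". Neither section says whether the second step carries a penalty or any shrinkage. Both sections plan a bootstrap with 1,000 resamples. Section 2.6 says that it will correct performance for optimism, and section 2.7 includes calibration among the measures assessed.

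**The concern.** The event range and the single ratio do not follow from the section's own inputs. A 30% rate in 210 children gives one expected count, and dividing it by 6, 7 or 8 gives three different ratios. The least favourable case, the plan's own maximum of 8 candidates, falls short of the figure claimed.

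This matters because the ratio is the only justification offered for the sample size, and it is offered as protection against overfitting. If the model is larger than the events support, and the coefficients are re-estimated after LASSO without shrinkage, predicted risks tend to be too high for high-risk infants and too low for low-risk infants. Performance of the prognostic model is a named secondary outcome (section 2.5.2). The primary outcome, incidence, is not affected.

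**Working it through.** **Inputs, all from section 2.6:** 300 enrolled; "10% mortality and 20% loss to follow-up"; 30% outcome rate; 6 to 8 candidate predictors.

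**1. Evaluable sample.** Adding the losses: 300 × (1 − 0.10 − 0.20) = 210, which reproduces the plan's figure. Applying them in sequence: 300 × 0.90 × 0.80 = 216, a difference of under 3%.

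**2. Events.** 210 × 0.30 = 63 (216 × 0.30 = 64.8). The stated upper figure needs 80/210 = 38.1%. Nor is 60–80 a sampling range around 63: the binomial standard deviation is √(210 × 0.30 × 0.70) = 6.6, so an approximate 95% range is 63 ± 13, or 50 to 76. The probability of 80 or more events at a 30% rate is 0.007.

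**3. Events per candidate predictor** (events ÷ candidates):

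| Candidates | 63 events (n = 210) | 64.8 events (n = 216) |
|---|---|---|
| 6 | 10.5 | 10.8 |
| 7 | 9.0 | 9.3 |
| 8 | 7.9 | 8.1 |

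**4. Where a flat 10 could come from.** It appears if the low ends are paired (60/6 = 10), the high ends are paired (80/8 = 10), or the midpoints are used (70/7 = 10). Crossing the stated ranges gives 60/8 = 7.5 to 80/6 = 13.3.

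**5. What a ratio of 10 would require with 8 candidates.** 80 events; 80/0.30 = 267 evaluable; 267/0.70 = 382 enrolled (267/0.72 = 371 if losses are applied in sequence). With 300 enrolled, the whole number of candidates that keeps the ratio at 10 or more is 6.

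**6. Likely overfitting at these sizes.** The documents give no signal strength, so it is assumed and varied.

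*Expected shrinkage S for a model fitted without selection* solves n = p / [(S − 1) ln(1 − R²/S)]. Here n = 210 and R² is the Nagelkerke value times its maximum at 30% prevalence, 1 − exp[2(0.3 ln 0.3 + 0.7 ln 0.7)] = 0.705.

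| Assumed Nagelkerke R² | 6 parameters | 8 parameters |
|---|---|---|
| 0.15 | 0.80 | 0.75 |
| 0.30 | 0.89 | 0.86 |
| 0.50 | 0.94 | 0.92 |

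*Simulation of LASSO followed by an ordinary logistic refit:* n = 210, 30% events, three true normal predictors with log-odds coefficients in the ratio 1 : 0.7 : 0.5, five-fold cross-validated LASSO, 60 data sets per setting (57 to 60 usable), calibration slope measured in 20,000 new subjects.

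| Signal (largest coefficient) | 6 candidates, mean slope | 8 candidates, mean slope |
|---|---|---|
| Weaker (0.5) | 0.77 | 0.67 |
| Stronger (1.0) | 0.84 | 0.85 |

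With 60 runs the small differences between 6 and 8 candidates should not be over-read. All four means are below 1, and the shortfall depends on signal strength.

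**The case against.** The best defence is that the plan is not far off. Six candidates lie inside its stated range and give 10.5. It says about 10, not more than 10, and names no minimum, so a reader who takes it to claim a ratio above 10 goes beyond the text. This stands, and it limits the point to 7 and 8 candidates and to the assumption that 10 is the minimum meant. It does not rescue the 60–80 events.

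A reader might also infer that many more than 8 candidates will enter LASSO, because section 2.1.2 speaks of "using a panel of early biochemical and imaging biomarkers". The text does not support this. That objective concerns risk factors for stroke and risk stratification, it gives no count, and section 2.6 expressly caps the candidates. The point therefore rests on 6 to 8.

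The phrase unpenalised refit is likewise an interpretation. Section 2.7 lists logistic regression as a separate step with no penalty mentioned, so an ordinary refit is the natural reading, but it is not stated.

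Finally, a bootstrap correction covering calibration is planned. A reader might infer that it will be run only on the refitted model and so endorse discrimination that does not exist. Nothing in the article says so, and how resampling is carried out is commonly left to a fuller analysis plan, which is not shown. What remains is narrower: optimism correction adjusts the reported performance and does not by itself shrink the published coefficients, and it is complete only if selection is repeated in each resample.

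**Conclusion.** The arithmetic error is certain on the plan's own inputs: 63 expected events, and a ratio of 10.5, 9.0 or 7.9. At the stated maximum of 8 candidates the ratio is about 21% below 10 (7.9 against 10). That the claimed minimum is missed at 7 and 8 candidates depends on that minimum being the customary 10, since the protocol gives no number.

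Overfitting is a likely consequence and not an established one. It depends on reading section 2.7 as an ordinary refit, and its size depends on how strong the predictors are: mean slopes of roughly 0.67 to 0.85 under the signals assumed. A ratio of 10.5 does not remove it either, since expected shrinkage with 6 parameters still ranges from 0.80 to 0.94. Shrinkage should therefore be specified whichever ratio is printed. The point deserves correction, but it concerns one secondary outcome and leaves the incidence estimate untouched.

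**What to change.** **Section 2.6.** Replace the event range and the ratio with one of the following:

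- *At a 30% outcome rate, 210 evaluable children give 63 expected events. At most 6 candidate parameters, counted before LASSO and fixed before outcomes are examined, will be considered (10.5 events per parameter).* A three-category predictor such as stroke subtype counts as two parameters.
- Or keep 6 to 8 candidates, give the ratio as 7.9–10.5, and delete the statement that it exceeds the recommended minimum.

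The first is preferable. Even so, 63 is an expectation: the chance of observing at least 60 events at a 30% rate is about 0.70, so the realised ratio may fall below 10.

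**Section 2.7.** State that the final model either keeps the LASSO coefficients or has its refitted coefficients multiplied by a bootstrap-estimated shrinkage factor. State also that the LASSO step, with its tuning, is repeated in each of the 1,000 bootstrap samples. If a fuller analysis plan already says this, one sentence of cross-reference is enough.

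**Cost.** Restated figures and some analysis code. Enrolment stays at 300. With the first option, the investigators give up up to two candidate predictors.

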Additionally, this study underscores the importance of multidisciplinary collaboration and the critical role of follow-up care in early rehabilitation. By emphasizing early diagnosis, intervention, and long-term follow-up, this research will contribute to a more refined and integrated management system for both perinatal medicine and pediatric care. The anticipated outcomes of this study not only hold promise for reducing the financial and emotional burdens faced by families but also offer significant improvements to national health standards, particularly by enhancing the quality of care for neonatal stroke across China.

However, it is important to acknowledge several limitations of this study. As an observational design, it cannot control for all potential confounding variables, limiting its ability to establish causality. The five-year follow-up period is prone to attrition bias, especially if dropouts are associated with disease severity or socioeconomic factors. Despite standardized protocols, the manual data entry across multiple institutions is vulnerable to inconsistencies and inter-rater variability. Furthermore, the findings may have limited generalizability outside of Shenzhen due to regional differences in demographics, healthcare access, and clinical practices. Moreover, during the 5-year enrollment and follow-up period, MRI protocols, neonatal care standards, and antiepileptic treatment strategies may evolve, potentially influencing outcomes. We will document any major practice changes and adjust analyses accordingly. These limitations should be considered when interpreting the study results and formulating future research directions.

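### The evaluable sample leaves out every child lost before 5 years, and no section says whether a diagnosis recorded at an earlier visit counts towards the 5-year composite

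*Protocol article*

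**What the plan says.** Five places in the protocol article bear on this.

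- **Secondary outcomes (2.5.2):** "Neurodevelopmental outcomes at 5 years were defined as a composite", built from Bayley-4C scores and clinical diagnoses. The primary objective (2.1.1) also names neurodevelopment at age 5.
- **Follow-up schedule (2.4.6, Table 1):** the row "Final outcome confirmation (cerebral palsy, cognitive impairment, epilepsy") has one tick, in the 5-year column. Bayley-4C, neurological examination and seizure/epilepsy assessment are ticked at all four visits.
- **Sample size (2.6):** "Total enrollment of 300 accounts, with 10% mortality and 20% loss to follow-up, and the understanding that the final evaluable sample will be approximately 210". The model is sized on this group: "approximately 210 evaluable participants would yield 60–80 outcome events".
- **Withdrawal and elimination (2.3.3, 2.3.4):** a child who does not complete scheduled follow-up is withdrawn. Elimination from the final analysis for missing data applies only when nothing at all was recorded, but serious deviations, including failure to comply with key procedures, also lead to elimination.
- **Discussion (3):** the follow-up is described as "prone to attrition bias, especially if dropouts are associated with disease severity or socioeconomic factors".

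The statistical analysis section (2.7) names LASSO, logistic regression and bootstrap validation. It names no analysis set for the 5-year composite.

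**The concern.** The outcome is tied to one late visit, and the sample size section treats anyone who misses that visit as contributing nothing. Yet three earlier visits collect the same kinds of information that make up the composite. A child with cerebral palsy confirmed at 18 months who then moves away has a known adverse status, but is among the 60 subtracted in 2.6. Section 2.3.4 points the other way, because that child does have recorded data. An analyst following the article cannot tell which applies.

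Two things are at stake. The first is the 5-year outcome rate: if families of more (or less) severely affected children are lost more often, the rate among attenders is off. The second is the prediction model, which has few events to spare and would not use outcome information already collected.

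**Working it through.** **Inputs from section 2.6.** Enrolment 300; mortality 10%; loss 20%; evaluable about 210; outcome rate 30% ("Assuming a 30% neurodevelopmental outcome rate at 5 years"); 60–80 events; 6–8 candidate predictors.

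**Step 1: reproduce the plan's figures.**
- Deaths: 0.10 × 300 = 30. Lost: 0.20 × 300 = 60.
- Evaluable: 300 − 30 − 60 = 210, exact. Applying the losses in sequence gives 300 × 0.90 × 0.80 = 216, also close to 210.
- Events: 0.30 × 210 = 63, inside 60–80.
- Events per variable: 63/6 = 10.5 and 63/8 = 7.9.

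The figure of 210 is reached only by removing all 60 lost children. Survivors number 300 − 30 = 270.

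**Step 2: events among the lost, at the plan's own rate.** 0.30 × 60 = 18. The documents do not say how many would be diagnosed before loss. If 25% to 100% were (assumed), 4.5 to 18 events would already be known.

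**Step 3: effect on the outcome rate.** Keep 30% among the 210 and let the rate among the lost be p, which the documents do not give. The rate in all survivors is (63 + 60p)/270.

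| p among the 60 lost (assumed) | Events among the lost | Rate in 270 survivors |
|---|---|---|
| 10% | 6 | 69/270 = 25.6% |
| 30% | 18 | 81/270 = 30.0% |
| 50% | 30 | 93/270 = 34.4% |
| 0% (extreme) | 0 | 63/270 = 23.3% |
| 100% (extreme) | 60 | 123/270 = 45.6% |

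At p = 30% there is no bias and the cost is precision. The standard error is √(0.3 × 0.7/210) = 3.2 points from attenders, against √(0.3 × 0.7/270) = 2.8 points if every survivor's status were known.

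**Step 4: check the obvious repair.** Suppose early diagnoses are counted but the other lost children are still dropped. With p = 30% and half to all of the 18 events found early:
- half: (63 + 9)/(210 + 9) = 72/219 = 32.9%
- all: (63 + 18)/(210 + 18) = 81/228 = 35.5%

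The true rate in this scenario is 30%, so adding positives alone biases the rate upward by about 3 to 5.5 points. A rule is needed for all 270.

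**The case against.** The strongest reply is that section 2.6 is a planning allowance. Inflating enrolment for attrition, with no credit for partly observed children, is ordinary and conservative, and it defines neither an analysis set nor a scoring rule. A reader might infer that a child diagnosed at 18 months or 3 years is discarded from the rate and the model. No passage says so. Section 2.3.4 suggests the opposite for missing data, and the follow-up conclusions module in 2.4.3 records final status without tying it to a visit. Missing-data handling may also sit in an analysis plan that is not shown. All of this stands against the stronger reading. It does not remove the conflict between sections: 2.3.3 withdraws the child, 2.3.4 appears to keep the child unless the missed visit is read as noncompliance, and 2.6 counts the child as not evaluable.

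A reader might also infer that the outcome rate will be too low because affected children leave more often. The documents give no direction or size for this, so the range in step 3 runs both ways. Step 3 also covers all events among the lost, not only those diagnosed beforehand.

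For the model, if loss depends on the outcome alone, logistic slopes are unaffected and only the intercept, hence calibration, shifts. Bias in predictor effects would need a more complicated loss pattern, which the documents do not establish.

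Finally, attrition is acknowledged, and section 2.4.2 gives retention measures. These may reduce the number lost but do not say how the lost are scored.

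**Conclusion.** The point holds as a conflict and a gap in how the 5-year composite is fixed; it is not a proven bias. Followed as written, sections 2.5.2, 2.6 and Table 1 amount to a complete-case analysis of 5-year attenders, leaving out 60 of 270 survivors (22%), although data that could inform their status are scheduled at three earlier visits.

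About 18 events lie in that group if the plan's 30% applies to it. The survivors' rate would lie between 25.6% and 34.4% if the rate among the lost were between 10% and 50%, which is an assumption. If loss is unrelated to outcome, the rate stays at 30% and only precision is lost. How much could be recovered depends on the share diagnosed before loss, which cannot be obtained from the documents. The matter should be settled before 5-year data are analysed.

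**What to change.** 1. Reconcile 2.3.3, 2.3.4, 2.6 and Table 1, so that it is clear whether a child who misses the 5-year visit stays in the analysis and whether a diagnosis confirmed earlier is used.
2. In 2.5.2 and 2.7, make all survivors the analysis set for the 5-year composite.
3. Multiply impute the missing composite from the baseline predictors and the 6-month, 18-month and 3-year results. Carry forward a specialist-confirmed cerebral palsy diagnosis made before loss as an adverse outcome. Use an earlier epilepsy diagnosis as an imputation predictor, not as an automatic event, because counting it outright would change the endpoint from status at 5 years to ever diagnosed.
4. Do not add early positives while dropping the other lost children (step 4).
5. Report two sensitivity analyses: 5-year attenders only, and epilepsy ever diagnosed counted as an event.

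The cost is plan wording and modest programming, with no extra visits. The imputation assumes that loss is explained by the recorded data, and the carry-forward rule assumes that a confirmed cerebral palsy diagnosis still stands at 5 years.

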### Statistical analysis plan

2.7

All analyses will be performed using SPSS (Version 27.0) and R (Version 4.4.1).
Descriptive Statistics: Continuous data will be presented as means ± SD (for normally distributed data) or as medians [IQR] (for non-normally distributed data). Categorical data will be analyzed using Chi-square or Fisher's exact tests.Incidence and Survival Analysis: Registry-based incidence and survival rates will be stratified by gestational age, sex, birth weight, and hospital level.Predictive Model Development:
Predictor Selection: LASSO regression will be used to identify potential predictors.Model Building: Multivariable logistic regression will identify independent factors associated with poor neurodevelopmental outcomes.Model Validation: Internal validation using bootstrap resampling (1,000 repetitions) will assess model performance (discrimination, calibration, and clinical utility).A two-sided *p*-value < 0.05 will be considered statistically significant.

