A central barrier to improving care is the profound lack of prospective, high-quality data on disease epidemiology and natural history (8). While countries such as the United Kingdom, Canada, and Australia have established national neonatal stroke registries to provide continuous, standardized monitoring of aetiology and outcomes (9, 10), such systematic data-collection initiatives are absent in China. Several other countries have successfully developed neonatal and infantile thrombosis registries; for example, the Italian Registry of Infantile Thrombosis (RITI) has provided valuable lessons regarding multicenter collaboration, data standardization, and the challenges of prospective data collection (9). Fragmented, retrospective studies and significant discrepancies in reported incidence rates characterize the existing evidence. For instance, a multicenter study in Beijing reported a rate of 1 in 2,660 (10), whereas a retrospective review across Shenzhen reported a much lower rate of 1 in 8,373 (10). These discrepancies likely reflect differences in case ascertainment (active surveillance vs. retrospective chart review), imaging protocols (universal MRI vs. selective cranial ultrasound), and referral patterns to tertiary centres, rather than true geographic variation in disease frequency. Furthermore, the long-term neurodevelopmental trajectory for survivors, a critical endpoint for families and healthcare systems, is poorly documented, and clinical management, especially for hemorrhagic and venous stroke subtypes, lacks consensus guidelines, leading to potentially inconsistent care.

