### Study design

2.2

This multicenter, prospective, observational cohort study aims to investigate the long-term neurodevelopmental outcomes of neonates with stroke. The study is planned to run for six years, from January 2025 to December 2030, in Shenzhen, China. The initial network comprises 22 collaborating hospitals, with Shenzhen Children's Hospital as the lead institution and Shenzhen People's Hospital as the primary coordinating center.

The study aims to recruit 300 neonates diagnosed with neonatal stroke, following them prospectively for five years to assess their neurodevelopmental trajectory. Additional hospitals may be included throughout the study period. A detailed study flow diagram is presented in Figure 1.

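### The only test stated for categorical data ignores clustering by hospital; applied to region or hospital level, its type I error would exceed 5%

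*Protocol article*

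**What the plan says.** The analysis section (2.7) has a general line under its descriptive statistics item: "Categorical data will be analyzed using Chi-square or Fisher's exact tests". The threshold for the whole section is "A two-sided *p*-value < 0.05 will be considered statistically significant". Apart from the LASSO and logistic prediction model, which targets poor neurodevelopmental outcome, no other between-group test is named. Section 2.7 mentions no hospital effect, robust variance or hospital-level analysis.

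Section 2.1.2 sets a secondary objective: "To analyze regional and institutional variations in the diagnostic, therapeutic, and rehabilitative management of neonatal stroke". Its results are meant to feed proposals for better and more uniform care. Hospital level appears in 2.7 only as a stratifier: "Registry-based incidence and survival rates will be stratified by gestational age, sex, birth weight, and hospital level".

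On size, section 2.2 says "The initial network comprises 22 collaborating hospitals" and "The study aims to recruit 300 neonates diagnosed with neonatal stroke", and allows further hospitals to join. The Introduction says that management, especially of the hemorrhagic and venous subtypes, "lacks consensus guidelines, leading to potentially inconsistent care".

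**The concern.** Most management variables are categorical (a treatment given or not, an investigation done or not), so the general line in 2.7 is the only stated method that fits the management objective.

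All infants of one hospital share its region and level. The chi-square or Fisher null is that every infant, in whichever hospital, has the same probability of receiving the treatment. The question for region or level is different: do groups of hospitals differ systematically, given that hospitals within a group may also differ? If hospitals have their own habits, the infant-level test can reject when region and level play no part.

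At stake is the use made of the result. A difference that comes from the practice of a few hospitals could be reported as a regional or level-of-care disparity and carried into the proposals for standardizing care.

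**Working it through.** **Inputs from the protocol article.** 300 infants and 22 hospitals (2.2), so the mean cluster size is m = 300/22 = 13.6; two-sided alpha 0.05 and the chi-square or Fisher test (2.7).

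**The plan's own figure.** Section 2.6 gives about 210 evaluable infants: 300 × (1 − 0.10 − 0.20) = 210, which reproduces. It concerns the 5-year outcome. No size calculation is given for comparing management, so all 300 are used below.

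**Assumptions, because the document gives none.** ICC 0 to 0.20; management rate 30%; two levels (11/11 hospitals), three levels (8/8/6) or six regions (4/4/4/4/3/3). Hospital sizes are equal (13 or 14 infants), proportional to 1/rank (82 down to 3), or one hospital with about 40% of cases (121).

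**Analytic check, two levels, equal sizes.** Design effect DE = 1 + (m − 1) × ICC; actual alpha = 2 × [1 − Φ(1.96/√DE)].

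| ICC | DE | Actual alpha |
|---|---|---|
| 0.01 | 1.13 | 6.5% |
| 0.02 | 1.25 | 8.0% |
| 0.05 | 1 + 12.6 × 0.05 = 1.63 | 12.5% |
| 0.10 | 2.26 | 19.3% |
| 0.20 | 3.53 | 29.7% |

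**Simulation of the chi-square test, no true region or level effect.** Hospital rates were drawn from a beta distribution with the given ICC, and hospitals were assigned to groups at random; 20,000 replicates. In each cell with ICC above 0, the lower end is equal sizes and the upper end uneven sizes.

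| ICC | 2 levels | 3 levels | 6 regions |
|---|---|---|---|
| 0 | about 5% | about 5% | about 5% |
| 0.01 | 6.5–8.4% | 7.0–9.2% | 8.0–10.6% |
| 0.02 | 7.7–11.8% | 9.2–13.5% | 11.7–16.4% |
| 0.05 | 12.4–20.8% | 15.8–26.4% | 23.4–35.4% |
| 0.10 | 20.1–32.3% | 26.9–42.1% | 44.4–58.5% |
| 0.20 | 30.3–48.0% | 43.3–60.8% | 69.6–81.2% |

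A 50% management rate gives nearly the same values. A second simulation with a 40% rate and other size patterns (4,000 replicates) agrees: with two levels, 13.5% (equal) and 18.3% (uneven) at ICC 0.05; with eight regions, 29.5% and 33.6%.

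**Fisher's exact test, two levels, equal sizes.** 3.8%, 6.8%, 11.4%, 17.3% and 29.4% at ICC 0, 0.02, 0.05, 0.10 and 0.20. It starts below 5% because it is conservative, so a very small ICC need not take it past the nominal level. It does not remove the inflation.

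**With the hospital as the unit.** A t-test on hospital proportions (11 against 11) had type I error of 4.7% to 5.2% for ICC 0 to 0.20 under all three size patterns. A permutation test reassigning whole hospitals had 3.1% to 6.5% (800 replicates). A mixed logistic model was not simulated. Because hospitals were assigned at random, these results do not cover a hospital size that is itself tied to level.

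**The case against.** A reader might infer that the protocol commits to testing regional and level differences by infant-level chi-square, and that false positives will therefore occur far more often than 5%. The document supports neither part. The sentence is a general one under descriptive statistics and is not tied to the management objective. That objective has no listed outcome in 2.5.2. Hospital level only stratifies incidence and survival, and stratifying is not testing. A fuller analysis plan may name another method. As to size, every input beyond 300 infants and 22 hospitals is assumed, including any dominant hospital, and at an ICC of 0.01 to 0.02 the inflation is modest. All of this stands and makes the point conditional.

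Two further objections deserve an answer.

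- **Institutional variation is the target.** This stands for differences among the individual hospitals. There, hospital-to-hospital variation is what is sought, and the stated tests suit the question.
- **The hospitals are close to a census.** The Introduction says more than 95% of the region's births occur in the 22 hospitals. If the aim were only to describe these hospitals in this period, rejection because of hospital differences would not be an error. But 2.1.2 uses the comparison to propose how care should be organized, and 2.2 lets more hospitals join. Both go beyond describing a fixed set.

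Nor does the Introduction's remark about inconsistent care prove that these 22 hospitals vary. It is general background, and the Discussion expects care to be coordinated across institutions. The objective itself treats variation between institutions as possible, without giving its size.

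**Conclusion.** The point holds in conditional form. The stated tests ignore clustering by hospital. If used for region or hospital level, the chi-square test exceeds its nominal 5% with any positive between-hospital variance: about 6.5% to 16% at ICC 0.01 to 0.02 and about 12% to 35% at ICC 0.05. The direction is firm; the size rests on the assumed ICC, number of groups and hospital sizes. Survival by hospital level is affected only if the strata are tested or given intervals.

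This goes beyond detail left to a later document, because the article names a test and that test does not suit one of its own objectives. It concerns a secondary objective only. The incidence outcome and the sample size are not touched.

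**What to change.** Add to section 2.7:

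- Any inferential comparison by region or hospital level (management; survival by level if strata are tested or given intervals) uses the hospital as the unit of inference. Options are a permutation test that reassigns whole hospitals, a t-test on hospital-level proportions, or a mixed logistic model with a random hospital intercept and a small-sample correction for 22 clusters.
- Chi-square and Fisher tests are kept for characteristics that vary within hospitals and for differences among individual hospitals.

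**Cost.** One or two sentences and some extra work in R, which is already planned; hospital information is already among the registry modules (2.4.3). No more patients or data are needed. The price is wider intervals and fewer significant differences. With many regions the hospitals run out: eight regions would leave 22/8 = 2.75 hospitals each. With fewer than about three per region, the regional comparison may have to be descriptive only, and 2.7 should say so.
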